### Phase 2: the feasibility study

#### The adapted GSD intervention on the web

The intervention is delivered through the platform MinJournal (‘My Chart’), developed at the Oslo University Hospital, Norway. It allows secure online communication between patients and healthcare professionals. The portal demands electronic identification by using BankID to reach the necessary security level 4, which is required when transferring sensitive data and medical journal information in the Norwegian healthcare system.

The worksheets applicable for T2DM are included in the web pages (see table 2). The intervention will consist of four e-consultations over 12–16 weeks. Information about the reflection sheets, together with information on how to communicate via the web portal, will be presented face to face at the first appointment with the nurse. Through the existing web-based platform, the subsequent four e-consultations will allow for communication between patients and nurses. The platform allows the participants to fill in the reflection sheets using their own words and drawings to express and reflect on their experiences and difficulties with diabetes management in daily life as well as to formulate behavioural goals and plans to achieve improved self-management. It also permits feedback from the nurses on these reflections, goals and plans via secure emails. Each person will be able to access the web-based programme from his or her own computers or other electronic devices.

#### Participants

In addition to the four nurses participating in the modelling phase, four new GSD-trained nurses will pilot the feasibility study (n=8). One of these four had formal postgraduate education in diabetes care, whereas the others had long experience in working with adults with T2DM. To obtain a varied picture of how the participants perceive the GSD programme, each nurse will recruit five patients with T2DM (n=40) from their general practices to participate in the web-based intervention. In addition to the inclusion criteria used in the modelling phase, participants are required to have access to the internet and Bank ID. Patients with cognitive impairment and/or severe comorbidity that would interfere with participation in the intervention will be excluded from the study.

#### Data collection and outcomes

This phase will employ quantitative and qualitative assessments of the feasibility of the recruitment strategies, programme acceptability and satisfaction, as well as evaluation of the measures to be used in the evaluation study (table 1). The elapsed time to fill out the questionnaires, accuracy of biographic and clinical variables and handling of the format will especially be assessed. The qualitative approach includes individual interviews with patients at the end of the intervention. On the basis of findings from the questionnaires and the interviews, we will determine features of the intervention components to be valuable and those in need of further development. This information, together with recommendations from the expert group, will be used to finalise the intervention for use in the third phase of the study (see table 1).

#### The quantitative approach

Data will be collected at baseline and at the end of the intervention using self-reported questionnaires.

##### Primary outcomes

Self-reported goal attainment questionnaire. The questionnaire developed by the research team will assess to what degree the patients have achieved diabetes goals with the following two items: (1) What were your change goals? and (2) To what degree have you achieved your goals?

The 13-item Patient Activation Measure (PAM). PAM developed by Hibbard *et al*^39^
^40^ will assess patient knowledge, skills and confidence in self-management of the patient's health and chronic conditions. The total score ranges from 0 to 100 (best).^41^ PAM has been validated in a previous Norwegian study.^42^

##### Secondary outcomes

The Health Care Climate Questionnaire (HCCQ), a six-item scale based on the original 15-item HCCQ,^43^
^44^ will measure the patients' perceptions of the degree to which they perceive autonomy support from healthcare providers.^43^
^45^ Each item is scored on a seven-point scale ranging from ‘strongly disagree’ to ‘strongly agree’. Higher scores indicate greater autonomy support from healthcare practitioners.

The degree of competence perceived by patients in managing diabetes will be assessed by using the four-item Perceived Competence for Diabetes (PCD) scale.^44^
^46^ The items have a seven-point Likert scoring format ranging from ‘not at all true’ to ‘very true’. Higher scores indicate a better perceived competence.

The 21-item Treatment Self-Regulation (TSRQ) scale developed by Ryan and Connell^47^ will measure the degree to which a person's motivation for a particular behaviour or set of behaviours is relatively autonomous, controlled or amotivated. The scale has been modified and adapted to assess various health behaviours.^48^

The 20-item Diabetes Management Self-Efficacy Scale (SE-T2DM) developed by Bijl *et al*^49^ will assess diet, feet control, medical treatment/control and exercise ability expectations. The respondents are asked to indicate their ability expectations on a five-point Likert scale ranging from ‘no, definitely not’ to ‘yes, definitely’. Higher scores represent greater expectations of the ability to perform necessary self-management activities.

The 14-item Summary of Diabetes Self-Care Activities (SDSCA)^50^ will assess self-care activities of people with diabetes such as general diet, specific diet, exercise, blood glucose monitoring, foot care and smoking. The instrument has extensively been used in diabetes research and has shown satisfactory reliability and validity.^50^ The respondents are asked about the frequency of performing the different self-care activities over the preceding 7 days. Scores range from 0 to 7 days; higher scores indicate greater frequency of performing self-care activities.

Emotional well-being will be assessed by using the WHO 5-item Well-Being Index (WHO-5).^51^
^52^ It is conceptualised as a unidimensional concept that contains five positively worded items. The degree to which these positive feelings were present in the past 2 weeks is scored on a six-point Likert scale ranging from 0 (not present) to 5 (constantly present).

Diabetes-specific distress will be assessed using the 17-item version of the Diabetes Distress Scale (DDS).^53^ The DDS has four subscales: emotional burden (five items), physician-related distress (four items), regimen distress (five items) and diabetes-related interpersonal distress (three items). The responses are on a scale (1–6) from ‘not a problem’ to ‘a very serious problem’. The scale has been validated in a previous Norwegian study.^54^

In addition, clinical parameter, such as HbA1c, will be measured by a blood sample at the GP office at baseline and at the end of the intervention. Self-reported height and weight (for body mass index calculating) and medical treatment will be collected as well. The accessibility and practice of the web-based portal will be measured by asking participants to write down the number of log-ons, time spent on filling the reflection sheets, time spent on e-consultations and the number of feedbacks from the nurses.

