#### Outcome assessments

Measurements are scheduled at three time points: at baseline, 12–16 weeks later at the end of the intervention and 6 months after finishing the intervention.

The patient-reported outcome measures to be collected during this evaluation study will be finalised during the feasibility study, but are likely to be the same as described in the feasibility study. Regarding the goal attainment measure, we expect that the intervention group will report having more goals, more ambitious goals and more progress towards attaining their goals. Other hypothesised benefits of the intervention include increases in PAM scores on patient activation, HCCQ scores on autonomy support, PCD scores on competence, TSRQ scores on autonomy and control, SE-type 2 scores on self-efficacy, SDSCA scores on self-care activities, WHO-5 scores on emotional well-being and decrease in DDS scores on diabetes distress. Clinical outcomes described in the feasibility study (ie, HbA1c) will also be collected at all three time points. We predict reductions in these outcomes relative to the control group.

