#### Data analysis

The quantitative data will be analysed using SPSS V.22 (IBM Corp, Armonk, New York, USA). Descriptive statistical analyses will include frequencies, means, SDs and CIs. The effect of the intervention on outcomes will be analysed by regression analyses with the following covariates: baseline scores, age and gender.

A supplementary analysis will assess whether patient-determined goals predict change on outcomes, that is, whether patients' change goals for particular self-care activities or psychological outcomes predict greater improvements on those outcomes (eg, for analysis of frequency of blood glucose self-monitoring, we will assess the potential impact of each patient's goal, if any, for blood glucose self-monitoring). We will also explore the possibility of pooling outcome results according to whether a patient had a goal to improve that outcome, for example, estimating the pooled effect size for change in each patient's primary chosen goal.

Additional analyses will assess patient usage of and satisfaction with the intervention tools, as well as facilitators and barriers to adoption of the web-based GSD, including the quality of the communication via secure messages with the nurses. We will also examine the nurses' perceived facilitators and barriers to the adoption of the web-based GSD.

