## Discussion

In this study protocol, we have described a complex intervention design for modelling, assessing feasibility and evaluating a GSD intervention. While the first two phases of this study will provide information on designing the intervention and its acceptability, the third phase will assess the effect of this systematically developed intervention on health outcomes such as patient activation, psychological outcomes, self-management behaviours and clinical outcomes. Moreover, we will identify factors that relate to the website use and its effectiveness in order to guide future web-based intervention development and implementation. We will gain insights into the participants' experiences of using the web-based programme at home, in their own time and hopefully increasing flexibility in everyday life.

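### Phase 2 measures portal use only by patients' own written tallies, although sheets and nurse feedback are created in an identified platform; platform or nurse counts would be a cheap, sounder measure for phases 2 and 3

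*Protocol article*

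**What the plan says.** **The measure.** In the protocol article, Phase 2, Secondary outcomes, use of the portal "will be measured by asking participants to write down the number of log-ons, time spent on filling the reflection sheets". Time on e-consultations and number of nurse feedbacks complete the list. The list does not include how many e-consultations or sheets were completed. Under The quantitative approach the same phase states: "Data will be collected at baseline and at the end of the intervention using self-reported questionnaires". The individual interviews add qualitative information on adoption, but no counts.

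**The platform.** Under The adapted GSD intervention on the web, patients fill in the reflection sheets on one hospital-developed platform. Access is personal: "The portal demands electronic identification by using BankID". Of the platform the article adds: "It also permits feedback from the nurses on these reflections, goals and plans via secure emails".

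**Phase 3.** Under Outcome assessments, the patient-reported measures are to be finalised during phase 2 but "are likely to be the same as described in the feasibility study". Under Data analysis, "Additional analyses will assess patient usage of and satisfaction with the intervention tools"; no source for the usage data is named. The Discussion says that "we will identify factors that relate to the website use and its effectiveness", with the purpose of guiding later web-based development and implementation.

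**The concern.** The article names a method here, so this is not a matter of detail left out of a condensed text. The named method is weaker than one that appears to be close at hand.

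- **Recall.** Patients are asked to count, over 12–16 weeks, events such as nurse feedbacks that arise within the platform and that the nurse has also seen.
- **Selective return.** The tally is missing for anyone who does not hand it in. Patients who used the portal little are plausibly less likely to do so.
- **Unit of exposure.** The programme consists of four e-consultations, yet the tally asks for time spent on them and not for how many were done.

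What is at stake is the description of use in the 40 phase 2 patients and, if the same tally is used in phase 3, the usage analyses there. A null phase 3 result would be harder to read, because a programme that does not work and a programme that was not used would be difficult to tell apart.

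**Working it through.** **Figure in the plan.** The article gives no figure for usage, for return of the tally or for its accuracy, so there is nothing on this point to reproduce. The one computable design figure, 72 per group for 6 PAM points with SD 11.1, 90% power and 5% significance, does reproduce: 2 × (1.960 + 1.282)² × 11.1² / 6² = 71.9, rounded up to 72 (two-sided). It does not depend on how use is measured.

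**Step 1: effect of non-return on mean use.** Let a share r return the tally with mean use m_R, and let the others have mean use m_N. The true mean is r·m_R + (1 − r)·m_N, so the reported mean is too high by (1 − r)(m_R − m_N). This is zero if return is unrelated to use and positive if low users return less often.

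**Step 2: effect of recall error on the use–outcome slope.** With random recall error of variance s², the slope of outcome on recorded use shrinks by the factor var(U) / (var(U) + s²), where U is true use.

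**Step 3: illustration by simulation (400,000 simulated patients).** Only the SD of 11.1 comes from the article (Sample size calculation). The rest are assumptions:

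- True log-ons are Poisson with a gamma-distributed mean (shape 1.5, mean 8); simulated mean 7.99, SD 7.10.
- Outcome Y = 6 + 0.5 × (U − 8) + error with SD 11.1; simulated slope 0.506.
- Recall error is normal with mean zero and SD 0, 2 or 4.
- Return of the tally is complete; or has logit −0.5 + 0.3U (38% at no log-ons, 87% at eight); or has logit −0.5 + 0.3U + 0.05(Y − 6).

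| Return of the tally | Share returned | Mean recorded use | Slope, recall SD 0 | SD 2 | SD 4 |
|---|---|---|---|---|---|
| Complete | 1.00 | 7.99 | 0.506 | 0.469 | 0.384 |
| Depends on use | 0.76 | about 9.55 | 0.504 | 0.468 | 0.387 |
| Depends on use and outcome | 0.74 | about 9.7 | 0.385 | 0.358 | 0.297 |

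The first row agrees with step 2: 0.506 × 50.4 / (50.4 + 4) = 0.469, and 0.506 × 50.4 / (50.4 + 16) = 0.384.

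**Reading the table.**

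- Mean use is overstated by 9.55 / 7.99 = 1.195, about 20%, when return depends on use, and by 9.7 / 7.99 = 1.21 when it also depends on outcome. With complete return and recall error of mean zero there is no overstatement.
- Loss of low users alone leaves the slope practically unchanged (0.504 against 0.506).
- The slope is biased by recall error, by return that also depends on outcome, or by both.

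**The case against.** The strongest reply is that the quoted measure belongs to a 40-patient feasibility study with descriptive statistics, part of whose task is to evaluate the measures for phase 3. The phase 3 usage source is not stated, and a condensed article may leave it to the full protocol. This stands: carry-over into phase 3 is a possibility, not something the article says.

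A reader might infer several stronger things that the article does not support:

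- **That non-users necessarily go missing.** A non-user who returns the record can write zero, and a patient who kept a running log may have entries before leaving. Only non-return loses data.
- **That 20% of phase 2 patients will have no usage data.** The 20% dropout is an allowance in the phase 3 sample size. No rate is given for phase 2 or for return of the tally.
- **That completion of the four e-consultations would be overstated.** The tally does not list that count, and nothing says completion would be taken from patients' notes.
- **That use and outcome always share one self-report at one time.** HbA1c is a blood sample, and phase 3 also measures outcomes 6 months after the programme.
- **That an objective of relating use to effect cannot be met without bias.** The stated aim contains no such objective, the Discussion sentence speaks of factors related to use and effectiveness, and no model linking use to outcome is given. The table also shows that loss of low users alone need not bias a slope.

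It is also fair that platform access is not described, and that the two time items would remain self-reported in any case. None of this makes the tally a good way to count sheets or feedbacks that pass through the platform.

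**Conclusion.** The point holds in a limited form. Patients' written tallies are the only quantitative measure of use that the article describes, and they are a weak choice for items created inside an identified platform. Phase 2 mean use is likely overstated if low users return the tally less often. If the tally is carried into phase 3, the usage analyses, and any work on factors related to use and effectiveness, would be vulnerable to recall error and selective return.

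The size cannot be fixed from the documents. On the assumed inputs, mean use was overstated by 0 to about 21%, and the slope lay between 0.30 and 0.51 against a true value of about 0.51. Systematic over- or under-counting was not modelled and would shift the mean directly.

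This is a low-cost improvement to a supporting analysis. The primary PAM comparison and the sample size are not affected.

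**What to change.** For every enrolled intervention patient, including those who drop out, take these from the platform:

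- reflection sheets completed;
- e-consultations completed (0–4);
- nurse feedbacks sent;
- log-ons, where the platform records them.

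If export is not possible, the nurse counts sheets, e-consultations and feedbacks from the patient's thread. Keep the patient's own record only for time spent. Name these counts as the usage measure in phases 2 and 3, and use e-consultations completed as the exposure if use is related to outcome.

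The cost is a data extract or a small nurse count, and a consent line that permits it. It depends on access to the platform, which the article does not describe. Patients have less to record. Phase 2 is underway and meant to settle the measures, so the change fits before phase 3 starts.

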#### The qualitative approach

The intervention process, such as facilitators and barriers to the adoption of the web-based GSD, including the quality of the communication via emails with the nurses, will be studied. All participants in the GSD intervention will be invited to take part in individual interviews. The interviews will use a semistructured interview guide developed by the research team, and they will be digitally audio-recorded and transcribed verbatim.

#### Data analysis

Quantitative data will be analysed using SPSS V.22 (IBM Corp, Armonk, New York, USA). Descriptive statistics will include frequencies, mean value, SD and CIs. Qualitative content analysis^38^ will be used to analyse the data from the interviews.

### Phase 3: the evaluation study

#### Quasi-experimental design

The effectiveness of this phase will be evaluated in a quasi-experimental design with one intervention and one control group. We hypothesise that a web-based GSD intervention will result in improvements in self-management behaviours and HbA1c compared with regular care in general practice.

#### Recruitment and data collection

The study will be carried out in general practices in the western part of Norway. To accomplish the requirement of trained GSD nurses, trained nurses working in general practices will conduct the GSD intervention. Participants with T2DM to be assigned to the intervention group will therefore be recruited from the practices where the nurses are working. Participants assigned to the control group will be recruited from other general practices with employed registered nurses without the GSD training. They will continue with their regular consultations in general practice. Inclusion and exclusion criteria are the same as described for the feasibility study.

All patients considered eligible for the study will be invited by mail to participate. Those who agree to participate and return a written informed consent will be enrolled and the nurse at each selected general practice will then make an appointment with the patient to start the GSD intervention.

#### The intervention

Based on findings from the feasibility study, refinements of the web-based intervention will be made via ongoing discussions with the research team, user representatives and diabetes nurses before deciding on the final application to the web. We intend to retain the essentials of the GSD approach and the selected worksheets addressing central GSD issues. In addition, we plan to base our intervention on the five consultations with the nurse assessed in the feasibility phase; the first appointment face to face, then the subsequent four e-consultations with selected structured worksheets aiming to improve diabetes self-management and HbA1c through patient activation, enhanced self-management competence and autonomy.

#### Outcome assessments

Measurements are scheduled at three time points: at baseline, 12–16 weeks later at the end of the intervention and 6 months after finishing the intervention.

The patient-reported outcome measures to be collected during this evaluation study will be finalised during the feasibility study, but are likely to be the same as described in the feasibility study. Regarding the goal attainment measure, we expect that the intervention group will report having more goals, more ambitious goals and more progress towards attaining their goals. Other hypothesised benefits of the intervention include increases in PAM scores on patient activation, HCCQ scores on autonomy support, PCD scores on competence, TSRQ scores on autonomy and control, SE-type 2 scores on self-efficacy, SDSCA scores on self-care activities, WHO-5 scores on emotional well-being and decrease in DDS scores on diabetes distress. Clinical outcomes described in the feasibility study (ie, HbA1c) will also be collected at all three time points. We predict reductions in these outcomes relative to the control group.

#### Data analysis

The quantitative data will be analysed using SPSS V.22 (IBM Corp, Armonk, New York, USA). Descriptive statistical analyses will include frequencies, means, SDs and CIs. The effect of the intervention on outcomes will be analysed by regression analyses with the following covariates: baseline scores, age and gender.

A supplementary analysis will assess whether patient-determined goals predict change on outcomes, that is, whether patients' change goals for particular self-care activities or psychological outcomes predict greater improvements on those outcomes (eg, for analysis of frequency of blood glucose self-monitoring, we will assess the potential impact of each patient's goal, if any, for blood glucose self-monitoring). We will also explore the possibility of pooling outcome results according to whether a patient had a goal to improve that outcome, for example, estimating the pooled effect size for change in each patient's primary chosen goal.

Additional analyses will assess patient usage of and satisfaction with the intervention tools, as well as facilitators and barriers to adoption of the web-based GSD, including the quality of the communication via secure messages with the nurses. We will also examine the nurses' perceived facilitators and barriers to the adoption of the web-based GSD.

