#### Sample size calculation

In GSD-like interventions, identification of a primary outcome differs from a traditional intervention study in that each individual participant (rather than the study director) determines the goals of the intervention. In essence, different patients have different primary outcomes. Nevertheless, for purposes of calculating power, a primary outcome must be identified. Since GSD is designed to increase patient involvement in goal selection and behaviour change, we have selected patient activation as the primary outcome. Therefore, change in patient activation is the primary end point as measured by the PAM scale total score. According to Steinsbekk,^55^ a detected difference in PAM score of six points (from 66.4 to 72.4) (SD 11.1) with 90% power and 5% significance level, the sample size must be 72 in each group. Given an expected dropout rate of 20%, we will include at least 172 patients in our study, 86 patients in each group.

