Possible limitations, especially those related to our evaluation study in the third phase, include the fact that assignment of patients to the intervention and control groups will not be random. This sampling, therefore, requires cautiousness about drawing inferences and conclusions from the data. In addition, the power of the study to assess improvement on any single outcome is reduced by the fact that only a subset of patients will have any particular outcome as a goal of their participation. In effect, the evaluation study can be thought of as a set of substudies, one for each outcome. However, our analyses will be designed to compensate for this departure from the top-down, researcher-driven design used in traditional non-personalised interventions. Finally, long-term (ie, > 6 months) effects of the web-based GSD intervention will not be assessed in this study. However, if this intervention is judged effective in the current study, this should provide the information necessary to conduct a definitive study of its long-term effects.

To the best of our knowledge, this will be the first study examining the GSD intervention adapted to a web-based version for adults with T2DM in general practice. We therefore expect that the results of this study will add significantly to the body of knowledge regarding web-based interventions for improving self-management among people with T2DM.

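### The two groups are formed by whole practices, but the sample size and the named regression treat the 172 patients as independent

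*Protocol article*

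**What the plan says.** Under Recruitment and data collection (phase 3), the protocol forms the groups by practice. For the intervention: "Participants with T2DM to be assigned to the intervention group will therefore be recruited from the practices where the nurses are working". For the control: "Participants assigned to the control group will be recruited from other general practices with employed registered nurses without the GSD training". Strengths and limitations confirms that "assignment of patients to the intervention and control groups will not be random".

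The Data analysis section gives the model for the between-group comparison: "The effect of the intervention on outcomes will be analysed by regression analyses with the following covariates: baseline scores, age and gender".

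The Sample size calculation section states that "change in patient activation is the primary end point as measured by the PAM scale total score". It bases the size on "a detected difference in PAM score of six points (from 66.4 to 72.4) (SD 11.1) with 90% power and 5% significance level" and concludes that "the sample size must be 72 in each group". Enrolment is then set at 86 per group (172 in all) for 20% dropout.

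The protocol does not mention clustering, an intracluster correlation, a design effect or the number of phase 3 practices. The limitations cover non-random assignment and patient-chosen goals, but not clustering.

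**The concern.** The group indicator is the same for every patient in a practice. In the intervention group, one nurse also delivers the face-to-face appointment and the four e-consultations to all of her patients. Patients of the same practice share staff, routines and catchment. Some outcomes are ratings of the provider, such as autonomy support on the HCCQ and physician-related distress on the DDS. Positive correlation within practices is therefore to be expected.

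When group varies only between practices, the precision of the group comparison depends on how many practices there are as well as how many patients. A regression that counts each patient as an independent observation then gives confidence intervals that are too narrow and p-values that are too small. This would affect PAM, SDSCA, HbA1c and every other between-group outcome with residual within-practice correlation. The stated power would also describe a different design from the one planned.

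**Working it through.** **Inputs from the protocol.** Difference 6 points, SD 11.1, alpha 5% (sidedness not stated; two-sided reproduces the figure), power 90%, 72 per group before dropout, 86 per group enrolled, 20% dropout.

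**Assumptions, because the protocol gives no figures.** ICC 0.01, 0.02, 0.05 or 0.10. Eight practices per group: the only guide is the eight GSD-trained nurses in the feasibility study, so other counts are shown below. Equal numbers per practice.

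**Step 1: the plan's own figure.** For independent patients, n = 2 × (1.960 + 1.2816)² × 11.1² / 6² = 71.9, so 72 per group. The match is exact, so the calculation contains a design effect of 1.

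**Step 2: patients analysed.** 86 × 0.8 = 68.8 per group, or 68.8 / 8 = 8.6 per practice.

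**Step 3: formulas.**
- Design effect: DE = 1 + (8.6 − 1) × ICC.
- Real two-sided error of the test that ignores clustering: 2 × [1 − Φ(1.96 / √DE)].
- Power: noncentral t with SE = 11.1 × √(2 × DE / 68.8) and 2 × 8 − 2 = 14 degrees of freedom.
- Power with baseline adjustment: the same, with SD 11.1 × √(1 − 0.5²), assuming a baseline–outcome correlation of 0.5.

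**Step 4: results for 8 practices per group.**

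| ICC | DE | Real error at nominal 5% | Power, unadjusted | Power, baseline r = 0.5 |
|---|---|---|---|---|
| 0.01 | 1.08 | 5.9% | 81% | 91% |
| 0.02 | 1.15 | 6.8% | 78% | 89% |
| 0.05 | 1.38 | 9.5% | 71% | 83% |
| 0.10 | 1.76 | 14% | 60% | 73% |

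**Step 5: sensitivity to the number of practices, at ICC 0.05.**

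| Practices per group | DE | Real error | Power, unadjusted | Power, baseline r = 0.5 |
|---|---|---|---|---|
| 4 | 1.81 | 14.5% | 51% | 62% |
| 6 | 1.52 | 11.2% | 64% | 76% |
| 12 | 1.24 | 7.8% | 78% | 88% |
| 16 | 1.17 | 6.9% | 81% | 91% |

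**Step 6: how much of the power loss is clustering.** Take 8 practices per group without baseline adjustment. Power is 90.0% at 72 patients and 88.7% at 68.8 (both normal approximation). It is about 84% at 68.8 with 14 degrees of freedom and ICC 0. So about 6 points are lost to dropout and degrees of freedom before any correlation enters. The design effect then takes it from 84% to 81% at ICC 0.01, to 71% at 0.05 and to 60% at 0.10.

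**Step 7: the design effect alone, with the full 72 analysed.** With 9 patients per practice and the normal approximation that the plan itself appears to use, power is 87.7%, 85.3%, 78.3% and 67.6% for the four ICCs.

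**The case against.** The strongest objection is that the protocol article is condensed. It speaks of regression and lists covariates, but it does not say ordinary least squares and does not rule out a random effect or cluster-robust errors in an analysis plan that is not shown. That is fair, and such a plan could repair the model. It could not repair the sample size and the 90% power, which are fixed in this text with a design effect of 1. The model as written also has nothing that acknowledges practice.

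Second, the power figures mix several losses, and baseline adjustment offsets some of them. This stands. About 6 points come from dropout and degrees of freedom, and at ICC 0.01 to 0.02 adjustment could bring power back to about 90%. With 16 practices per group it could do so at ICC 0.05. But the sample size calculation claims no such gain, and the protocol does not say whether SD 11.1 refers to the score or to its change.

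Third, the ICC and practice count are assumed, and one design effect is applied to both groups although only the intervention group has a nurse-delivered programme. The size is therefore uncertain. The baseline score may also absorb part of the between-practice variation, so the ICC that matters is the residual one. Any positive residual value still leaves the standard errors too small.

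Fourth, the design is non-randomised and the protocol already urges caution. Confounding of practice with group is a separate problem that a random effect does not solve. It does not excuse invalid standard errors.

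**Conclusion.** The concern holds. The protocol assigns group by practice, sizes the study as if patients were independent, and names a model without practice or nurse. The direction is certain for any positive residual within-practice correlation: real type I error is above 5%, and power on the plan's stated inputs is below 90%.

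The size cannot be fixed from the document. With 8 practices per group and ICC 0.01 to 0.10, the real error runs from just above nominal to nearly three times it. The power shortfall is less certain than the error inflation: it could be negligible if the ICC is low and baseline PAM is a good predictor, and serious if practices are few. Because the primary comparison is affected, this should be settled before phase 3 data are collected.

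**What to change.** - **Model.** Fit the phase 3 outcomes as linear mixed models with a random intercept for practice (or nurse) and small-sample degrees of freedom such as Satterthwaite, keeping baseline score, age and gender. MIXED in the named SPSS version can fit the random intercept.
- **Power.** In the Sample size calculation section, state the planned number of practices per group and replace the single 90% with power over a stated ICC range. Say whether SD 11.1 is for the score or the change, and whether baseline adjustment is counted.
- **Inputs.** Phase 2 (8 nurses with 5 patients each) can inform the SD and the correlation between baseline and end-of-programme PAM. It is too small to pin down the ICC.
- **Recruitment.** Aim for similar numbers per practice, and prefer more practices to more patients per practice. At ICC 0.05, the normal approximation for 90% power needs 72 × 1.40 = 100.8, so 101 analysed per group, if practices of 9 patients are added. With practices fixed at 8 per group it needs 72 × 0.95 / (1 − 72 × 0.05 / 8) = 124.4, so 125.

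**Cost.** One changed model statement, somewhat wider intervals and a less favourable power figure. Valid inference needs no extra patients or data. If the sponsor wants to keep 90% power across the ICC range, more practices may be needed; otherwise the lower figure should be reported openly. The random effect corrects the standard errors but does not remove confounding between practice and group.
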